### A Multi-Theory Model based on BCW and family health

2.5

Because family has an overarching role in individual wellbeing, and the strength of communities and society (36), the combination of the BCW and the Family Health theory provides a novel perspective and pathway for health behavior interventions. By applying the BCW theory from the individual level to the six domains of the Family Health, a Multi-Theory Model (shown in **Figure 4**) is formed, which can offer more effective intervention strategies for improving the health behaviors of individual family members as well as the family as a whole. The three levels of the BCW theory will be used to discuss how these two theories can be combined and used below.

**Figure 4 f4:**
[figure not shown]
Schematic diagram of a multi-theoretical model.

#### Expansion of the COM-B model in family health: the COM-FB model

2.5.1

The inner layer of the BCW theory is the COM-B model, which explores three components of behavior (B): capability (C), opportunity (O), and motivation (M). These components can be mapped to the six domains of the Family Health Theory framework, thereby extending the model to the family level and forming the COM-FB model. Specifically:

Capability (C): Family member health, Family health-related practices, and Family health resources of the Family Health theory specify requirements for capability. This includes physical capability (C-Ph), such as caring for patients, providing appropriate food, and regular monitoring, as well as psychological capability (C-Ps), such as disease knowledge and understanding.

Opportunity (O): Opportunity refers to environmental factors that facilitate behavior change, including social opportunities such as interpersonal relationships and physical opportunities such as time and resources. Family social context, Management of time and activities of the Family Health theory defines opportunities at the family level. This includes external opportunity (O-Ex), such as family safety and home environment, and internal opportunity (O-In), such as time allocation for work and family activities.

Motivation (M): Family relationships, interactions and beliefs of the Family Health theory addresses motivation at the family level. This includes automatic motivation (M-Au), such as family cohesion and a sense of belonging, and reflective motivation (M-Re), such as beliefs and values regarding caregiving.

#### Application of the nine intervention functions in family health

2.5.2

According to the BCW theory, once the family-level COM-FB model is established, specific intervention strategies can be designed based on the nine intervention functions: education, persuasion, motivation, coercion, training, restriction, environmental restructuring, demonstration, and empowerment. For example, teaching parents to improve disease awareness and understanding, training to improve the ability to take a low-Phe diet, and setting incentive mechanism to improve the enthusiasm of regular monitoring.

#### Application of external resources and policy support in family health

2.5.3

The outer layer of the BCW theory consists of seven policy categories, emphasizing the supportive role of external resources in enabling intervention functions. Therefore, after selecting the nine intervention functions, external resources can be utilized to facilitate their implementation. For example, society can distribute printed or electronic materials for education, relevant institutions can develop disease guidelines, governments can provide financial support such as medical insurance, and primary healthcare institution can offer more affordable and high-quality consultation services, making it easier for family to access health education resources.

### Development of mHealth intervention based on the Multi-Theory Model

2.6

The Multi-Theory Model, which was created by combining the BCW theory and the Family Health theory, will serve as the foundation for the study. Using the WeChat, a mobile health intervention program will be developed for families of PKU children (including the children and their parents’ caregivers, such as parents) to explore its effectiveness in the health management of PKU children, including metabolism, nutrition, and intellectual development. According to the specific stages of applying the BCW theory, the intervention strategies for PKU families are as follows:

#### Stage 1: examine the obstacles to changing behavior of PKU families based on the COM-FB model

2.6.1

C-Ps (Psychological Capability): Refers to the cognitive level of PKU children and their parents’ caregivers regarding phenylketonuria, including knowledge of the disease, specific requirements of a low-Phe diet, and the importance of regular monitoring. Currently, some parents of PKU children lack sufficient awareness of the importance of PKU health management, which is one of the main reasons for poor dietary and follow-up compliance.

C-Ph (Physical Capability): Refers to the skill level of PKU children and their parents’ caregivers in preparing and maintaining a low-Phe diet. At present, some parents’ caregivers lack professional training and are deficient in skills such as food pairing for a low-Phe diet, understanding ideal Phe intake, and supplementing other nutrients in daily feeding.

O-Ex (External Opportunity): Refers to the access of PKU families to external medical resources, including nearby medical institutions that conduct newborn PKU screening and regular blood Phe monitoring, professional physicians providing consultation services, and educational materials on PKU knowledge and skills training. Additionally, it includes the convenience of accessing information on Phe content in foods.

O-In (Internal Opportunity): Refers to the time and energy allocated by family members for the health management of PKU children, including the time distribution of parents’ caregivers and family communication. This is related to the level of importance family members place on the child and their compliance with health management. Currently, some parents have limited energy for the health management of their children, with insufficient attention paid to diet, follow-up, and growth and development monitoring, significantly affecting the effectiveness of PKU health management.

M-Au (Automatic Motivation): Refers to the cohesion, sense of belonging, and responsibility among family members, which serve as important internal driving forces for strict and continuous PKU health management.

M-Re (Reflective Motivation): Refers to the family’s trust in the effectiveness of health management for PKU children. Currently, some families hold pessimistic attitudes toward the intellectual development and quality of life of PKU children and lack confidence in the effectiveness of health management measures such as a low-Phe diet, greatly reducing their motivation for daily management.

#### Stage 2: select intervention functions

2.6.2

Based on the analysis of the main barriers to improving the behavioral impact on families of children with PKU in Stage 1, interventions are selected from the nine major intervention functions, combined with seven policy categories to facilitate their implementation.

Education: Provide printed or electronic PKU educational materials.

Persuasion: Professional physicians educate the parents’ caregivers of children with PKU based on PKU guidelines; Set up timed reminders for blood Phe monitoring.

Motivation: Provide feedback on daily dietary habits and regular monitoring progress; establish family reward mechanisms such as points, prizes, and honorary titles.

Training: Professional physicians train the parents’ caregivers of children with PKU on low-Phe dietary strategies based on PKU guidelines, including questions such as what to eat, how much to eat, and how to eat.

Environmental Restructuring: Improve accessibility to medical resources and information on food Phe content, including setting up convenient channels for consulting professional physicians, providing Phe content tables for common foods, and automated Phe content calculation tools.

Demonstration: Regularly organize family exchange meetings for PKU patients to share health management experiences.

Empowerment: Develop low-Phe dietary plans according to PKU guidelines; Conduct regular follow-up monitoring of blood Phe levels, nutrition, intellectual development, and quality of life in local medical institutions.

#### Stage 3: determine intervention content and implementation options—mobile health intervention based on the WeChat

2.6.3

Based on the analysis and selections from the previous two stages, and after comprehensively considering affordability, practicability, effectiveness acceptability, safety, and equity, the final decision is to utilize WeChat group chats for remote mobile health intervention. The group chat will incorporate the following four functions to achieve the seven interventions outlined in Stage 2:

*Health education module and real-time reminder function*. Through the WeChat group, educational materials in various formats (e.g., illustrations, videos) will be distributed weekly to provide PKU knowledge and health education. Topics include basic disease knowledge, the importance of health management, low-Phe diets, and regular follow-up monitoring. Personalized reminder notifications will also be set up to encourage timely completion of dietary records and regular medical check-ups.
*Diet uploading and phenylalanine content query function*. Parents will input the types and quantities of food consumed by their child each day into the WeChat group chat. The system will automatically calculate the daily Phe intake, notify parents if the intake exceeds the recommended limit, and provide adjustment suggestions. Additionally, the WeChat group will include a built-in food Phe database containing Phe content for common foods across three meals, along with recommended low-Phe meal combinations.
*Regular feedback and incentive mechanism*. The group chat will record the dietary logs and compliance status uploaded by parents. At the end of each month, virtual rewards such as badges and titles will be issued based on the monthly records to motivate parents to continue maintaining healthy management behaviors.
*Family interaction and online consultation function*. Parents can interact with other PKU families in the group chat to share health management experiences. Additionally, the group chat will offer an online consultation feature, allowing parents to seek advice from professional physicians in the group at any time.

### Health education materials

2.7

#### Sources of health education materials

2.7.1

The educational materials used for health education come from the Internet, including videos and illustrations. The illustrations are obtained from WeChat, Baidu Baike, Wikipedia, doctor’s Q&A, or domestic and international databases such as CNKI. The videos are primarily animations and are sourced from platforms such as WeChat and Baidu Baike. Case information is derived from Baidu documents or literature. All educational materials are required to be scientifically sound and supported by relevant references.

#### Screening of health education materials

2.7.2

All health education materials are examined and assessed by experts in the field of PKU, and screened based on expert feedback. Selected materials are compiled into a health education database. The database includes the article title, relevant links, source, and material type. To make it easier to create individualized treatment regimens for patients, these resources were divided into four major parts according to their principal content: disease knowledge, low-Phe diet, routine monitoring, and mental health.

### Outcomes

2.8

Primary Outcomes:serum phenylalanine and tyrosine levels in children with PKU.

Secondary Outcomes:

Nutritional indicators: Height/length (cm), weight (kg), head circumference (cm), the concentration of hemoglobin, prealbumin, albumin, complete blood count (red blood cells, white blood cells, platelets), serum iron, ferritin, and 25-Hydroxy vitamin D3.Intellectual development indicators: For children aged ≤6 years, professional physicians will use the 0–6 Years Child Developmental Behavior Assessment Scale for evaluation. For children aged >6 years, IQ will be assessed using the Chinese version of the Wechsler Intelligence Scale for Children, Fourth Edition (WISC-IV).

In addition, considering that the health management of children with PKU may impose psychological and quality-of-life burdens on their parents’ caregivers (37, 38), the study also focuses on the following indicators for parents’ caregivers: PKU disease knowledge, compliance, mental health, family health, and family atmosphere, etc. Specific details are as follows:

Changes in PKU knowledge.Changes in parental compliance with health management: Measured by the number of dietary Phe concentration logs and the number of blood tests during the intervention period (39).Impact of health management on parental mental health: Includes levels of anxiety and depression, self-efficacy, and parenting stress.Changes in the family environment of PKU children: Includes specific behavioral changes such as family communication and broader indicators such as family health.

Socio-demographic variables will be collected from patients at baseline. Clinical reagent testing and questionnaires will be conducted at baseline as well as at 3 and 6 months of follow-up, with data collection times shown in **Table 2**.

**Table 2 T2:** Data collection components and collection timeline.

Type of research	Data collection		Timepoint		
			0M	3M	6M
Quantitative research	Sociodemographic variables	Gender, age, parental education level, parental occupation, monthly household income per capita, only-child status, presence of other PKU patients in the family	✓		
	Anthropometric variables	Serum phenylalanine(Phe)and tyrosine(Tyr)levels, height/length (cm), weight (kg), head circumference (cm), the concentration of hemoglobin, prealbumin, albumin, complete blood count, serum iron, ferritin, and 25-Hydroxy vitamin D3	✓	✓	✓
	Intellectual development variables	For children aged ≤6 years, professional physicians will use the 0–6 Years Child Developmental Behavior Assessment Scale for evaluation. For children aged >6 years, IQ will be assessed using the Chinese version of the Wechsler Intelligence Scale for Children, Fourth Edition (WISC-IV)	✓	✓	✓
	PKU knowledge	Questionnaire: Changes will be measured by a self-designed PKU theory scale	✓	✓	✓
	Parents compliance with health management	Measured by the number of dietary Phe concentration logs and the number of blood tests during the intervention period	✓	✓	✓
	The level of anxiety and depression on parents	Questionnaire: A simplified version of the Anxiety Depression Scale (PHQ-4)	✓	✓	✓
	The level of self-efficacy on parents	Questionnaire: A simplified version of New General Self-Efficacy Scale (NGSES-SF)	✓	✓	✓
	The level of parenting stress on parents	Questionnaire: The Parenting Stress Index (PSI-SF-15) and the Guilt about Parenting Scale (GAPS)	✓	✓	✓
	Family communication	Questionnaire: A Short Form of the Family Communication Scale (FCS-SF)	✓	✓	✓
	Family health	Questionnaire: A Short Form of the Family Health Scale (FHS-SF)	✓	✓	✓

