**Methods:**

This single-center, single-blind randomized controlled trial will be conducted at the Inner Mongolia Maternity and Child Health Care Hospital in China from March to September 2025. Participants will include children with PKU and their parents’ caregivers, who will be randomly assigned to either the intervention group (receiving mHealth interventions via WeChat) or the control group (receiving routine health education). The intervention will include health education, dietary management, regular monitoring reminders, and online consultation services. The primary outcome will be the serum phenylalanine and tyrosine levels of the children. Secondary outcomes will include nutritional indicators, intellectual development indicators, and the caregivers’ health knowledge, compliance, and mental health. Data collection will occur at baseline and at 3 and 6 months post-intervention.

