### Sample size

2.3

The sample size was calculated based on the primary metabolic indicator, serum Phe concentration. This study is a randomized controlled trial, with the intervention group receiving mobile health interventions and the control group receiving regular health education. The sample size ratio between the two groups is 1:1. According to a randomized controlled trial on PKU children based on a mobile health app (35), the blood Phe concentration in the control group was 360 μmol/L, while that in the intervention group was 260 μmol/L, with a standard deviation of 100 μmol/L in both groups. Using a two-tailed test with α = 0.05 and β = 0.1, the power (1-β) was set at 90%. Calculations performed using PASS 15 indicated that a minimum of 23 participants per group was required. Accounting for a 10% attrition rate, each group was expanded to 25 participants, resulting in a total minimum sample size of 50 participants.

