## Statistical analysis

3

Statistical analysis will be performed using SPSS Statistics 26.0. Categorical data will be expressed as counts and percentages (n, %). Continuous data will be presented as mean ± standard deviation (x¯ ± s). The Mann-Whitney U test will be used to compare changes in each indicator between the two groups at 3 months and 6 months post-intervention relative to baseline. The Wilcoxon test will be employed to compare differences between the two groups at baseline and across four follow-up time points. Baseline demographic characteristics between the two groups will be compared using the chi-square test. A two-tailed test will be applied, and a P-value < 0.05 will be considered statistically significant.

If a reasonable amount of missing data is present, the data summary will indicate that the data are missing at random. In such cases, all analyses will incorporate multiple imputation procedures using baseline variables as auxiliary variables to address missing data. Linear regression and logistic regression will be selected for the imputation process, and the final analysis results will be combined to complete the imputation and analysis procedures.

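### Serum Phe and Tyr are both primary and each is tested at 3 and 6 months at P < 0.05 without ranking or adjustment, whereas the sample size plans a single Phe test

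*Protocol article*

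**What the plan says.** - **Outcomes (section 2.8).** The primary outcomes are "serum phenylalanine and tyrosine levels in children with PKU". The abstract agrees: "The primary outcome will be the serum phenylalanine and tyrosine levels of the children". Neither place ranks the two analytes, names a deciding visit, or says whether one or both must show an effect.
- **Statistical analysis (section 3).** The Mann-Whitney test will "compare changes in each indicator between the two groups at 3 months and 6 months post-intervention relative to baseline". The significance rule is general: "A two-tailed test will be applied, and a P-value < 0.05 will be considered statistically significant". No adjustment or order of testing is given.
- **Sample size (section 2.3).** "The sample size was calculated based on the primary metabolic indicator, serum Phe concentration". The inputs are means of 360 and 260 μmol/L and an SD of 100 μmol/L. The error rates are set by "Using a two-tailed test with α = 0.05 and β = 0.1", and "the power (1-β) was set at 90"%. The result is 23 per group, raised to 25 for 10% attrition. Tyr does not enter the calculation, and no visit is attached to the Phe values.

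**The concern.** The sections do not describe the same primary analysis. Outcomes and Statistical analysis together give two analytes at two visits, which is four between-arm tests at 0.05 each. Sample size plans for one.

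What this costs depends on a rule that the article does not give:

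- **Any one success counts.** The trial has up to four chances of a false-positive primary result, so the 0.05 used for sizing is not the error rate of the primary claim.
- **Tyr must succeed as well as Phe.** The false-positive risk is then controlled, but the chance of a positive trial depends on an outcome with no planned effect and no planned power.

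The same results could therefore be reported as a positive or a negative trial, depending on a choice made after they are known.

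**Working it through.** **1. Reproduce the stated sample size.** Inputs from section 2.3: difference 100, SD 100, two-sided α = 0.05, power 90%, ratio 1:1.

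- Normal approximation: n = 2 × (1.960 + 1.282)² × (100/100)² = 21.0, so 22 per group.
- Exact two-sample t-test (noncentral t): 22 per group gives 89.97% power and 23 gives 91.2%, so 23 per group.

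The stated 23 is reproduced. It is the size for one Phe comparison at two-sided 0.05.

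**2. Count the primary tests.** 2 analytes (section 2.8) × 2 visits (section 3) = 4 tests, each at 0.05.

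**3. Chance of at least one false positive if any one success counts, with no true effect anywhere.**

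- Four independent tests: 1 − 0.95⁴ = 0.185. The Bonferroni upper bound is 4 × 0.05 = 0.20.
- Correlated tests: the documents give no correlations, so these are assumed. Four two-sided normal tests were simulated, with the correlation between visits and the correlation between analytes set separately.

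| Correlation between visits | Analytes −0.3 | Analytes 0 | Analytes 0.3 | Analytes 0.5 |
|---|---|---|---|---|
| 0.3 | 17.8% | 18.1% | 17.7% | 16.9% |
| 0.5 | 16.9% | 17.3% | 16.9% | 16.2% |
| 0.7 | 15.7% | 16.1% | 15.7% | 14.9% |
| 0.9 | 13.2% | 13.6% | 13.2% | 12.5% |

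Changes at 3 and 6 months share one baseline value, so some positive correlation between visits is to be expected. If all three visits are equally correlated with equal variances, the two changes correlate 0.5, which is the second row.

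**4. The same check if Phe alone is taken as primary, at two visits.** Independent: 1 − 0.95² = 9.75%. With visit correlations of 0.3, 0.5, 0.7 and 0.9: 9.5%, 9.1%, 8.4% and 7.0%.

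**5. Power if Tyr must also succeed.** Completers: 25 × 0.90 = 22.5, taken as 22 per arm. The documents give no Tyr effect, so three values are assumed. Power is for a two-sample t-test at two-sided 0.05, with noncentrality d × √(22/2):

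| Assumed Tyr effect (SD) | Power for Tyr |
|---|---|
| 0.3 | 16% |
| 0.5 | 37% |
| 0.8 | 74% |

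The probability that both analytes succeed cannot exceed the Tyr figure.

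**6. Cost of keeping all four tests as primary.** Bonferroni gives 0.05/4 = 0.0125 per test. The same t-test calculation for Phe then needs 31 per group, or 31/0.90 = 34.4, so 35 with attrition. With 23 per group, power for Phe falls from 91% to 78%.

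**The case against.** **No section promises a 5% error rate across all primary tests.** This stands. The 0.05 in section 2.3 belongs to one Phe comparison, and the 0.05 in section 3 is a per-test threshold. A reader might infer that the plan states a 5% overall rate and breaks it. The text does not support that: inflation follows only if any one success counts, which is not stated. If all four tests had to succeed, the type I error would be at most 5%.

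**A condensed article may leave success rules and testing order to the full protocol or the SAP.** This stands in part. An SAP not shown here could add a hierarchy. But the article itself fixes two primary analytes, both test times and one common threshold, alongside a sample size for one test. The conflict lies in what is stated, and a hierarchy added later would change what is published here.

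**Section 2.3 already treats Phe as the lead outcome.** It does single Phe out, and this roughly halves the problem. It does not remove it: the abstract and section 2.8 keep Tyr as an equal primary outcome, and Phe alone is still tested at two visits with neither named.

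**The visit labels might seem to add a second ambiguity.** The abstract and section 3 label the visits as months post-intervention, whereas section 2.1 counts them from the start of the intervention. A reader might infer that the timing is uncertain. It is not: section 2.1 and the 0M/3M/6M columns of Tables 1 and 2 settle it. The label is an editorial matter and has no bearing on multiplicity.

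**Conclusion.** The point holds as a conflict between stated sections: up to four unadjusted primary tests where one was planned, and no single comparison that decides the trial.

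If any one success counts, the false-positive chance exceeds 5% in every setting examined. It is 18.5% for four independent tests, about 12.5% to 18% for assumed correlations of 0.3 to 0.9 between visits and −0.3 to 0.5 between analytes, and about 7% to 10% for Phe alone at two visits. If Tyr must also succeed, the error rate is not the issue. Power is then unplanned and ranges from 16% to 74% for Tyr effects of 0.3 to 0.8 SD.

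The correlations and the Tyr effects are assumptions. The Tyr range shows how far the answer depends on an effect that the plan does not give. It does not show that the trial is underpowered for Tyr. The Phe sample size itself is correct for the single test that it describes.

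**What to change.** Before outcome data by arm are seen, name one primary comparison: the between-arm comparison of serum Phe at one stated visit, two-sided 0.05. Phe is the analyte used for the sample size. Six months after the start, when the intervention ends, is a reasonable visit, but this is a choice to be made, because section 2.3 gives none.

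Make Tyr and the other Phe visit secondary, or test them in a pre-specified fixed order, going on only while each preceding test is significant. Use the same wording in the abstract, Outcomes, Sample size and Statistical analysis sections. Counting the visits from the start of the intervention throughout would be a harmless tidy-up at the same time.

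This restores 5% for the primary claim and leaves the 23 per group unchanged. It needs no extra families or measurements. The small cost is that Tyr and the other visit no longer count as stand-alone primary successes. Keeping all four as primary with Bonferroni would instead need 31 per group before attrition.

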### Trial design and setting

2.1

The research will be conducted at the Inner Mongolia Maternity and Child Health Care Hospital in China from March 2025 to September 2025, employing clinical reagent testing and internationally recognized scales for quantitative investigation.

The study population consists of families of children with PKU, who will be divided into two groups: Group A will be the mHealth intervention group, while group B was the control group. The intervention group will receive mobile health interventions through WeChat group chats. The control group, on the other hand, will simply get regular health education, which includes an oral presentation on PKU by a professional physician at the time of enrollment, educating the parents of PKU children on how to manage their diets low in phenylalanine. A printed handbook on PKU disease and daily management knowledge will also be given to them, but they won’t have access to online education and training, frequent reminders for monitoring, or online consultation services.

The intervention will last for 6 months, with clinical indicators, intelligence tests, and questionnaire surveys being conducted at baseline, as well as at 3 and 6 months after the start of the intervention to examine the effectiveness of the intervention on the health management of children with PKU. The flow chart of the study is shown in **Figure 3** and **Table 1**.

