### Study participants

2.2

The participants of this study are all PKU children and their parents’ caregivers, such as parents, who meet the inclusion criteria and have been screened by the Inner Mongolia Maternal and Child Health Care Hospital in China by the end of February 2025. Each participant will begin the formal intervention after being informed face-to-face by a hospital doctor and signing the research informed consent form. This study has been approved by the Ethics Committee of Inner Mongolia Maternity and Child Health Care Hospital, Hohhot, Inner Mongolia Province.

Inclusion Criteria:

Age: 0 ≤ age < 12 years, regardless of gender.The child must meet the diagnostic criteria for PKU as outlined in the Rare Disease Diagnosis and Treatment Guidelines (2019) and be confirmed as a PKU patient through genetic testing.The parents’ caregivers, such as the child’s parents, must have the ability to use WeChat and possess normal language communication skills.They must understand and agree to participate in the intervention, be willing to fully cooperate with the intervention measures and follow-up examinations, and sign the informed consent form.

Exclusion Criteria:

The parents’ caregivers do not have a regular contact method or are unable to use WeChat daily.The child or parents’ caregivers have other severe systemic diseases or significant physical functional impairments.The child or parents’ caregivers exhibit mental symptoms such as unclear consciousness, language expression difficulties, or uncooperativeness.The child or parents’ caregivers are taking any psychiatric medications.The child or parents’ caregivers are already participating in other clinical trials.Any other reasons deemed unsuitable for participation in the trial.

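### Raw growth change in children aged 0 to under 12 loses power to age, and two developmental instruments feed one test of change without a rule for combining them

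*Protocol article*

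**What the plan says.** Section 2.2 (Study participants) sets the age range: "Age: 0 ≤ age < 12 years, regardless of gender". Section 2.8 (Outcomes) lists the growth measures among the nutritional secondary outcomes as "Height/length (cm), weight (kg), head circumference (cm"), and Table 2 repeats them in the same units at 0, 3 and 6 months. The article mentions no z-score, percentile or other age standard.

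Intellectual development, also in section 2.8, is measured with one of two instruments: "For children aged ≤6 years, professional physicians will use the 0–6 Years Child Developmental Behavior Assessment Scale for evaluation", and "For children aged >6 years, IQ will be assessed using the Chinese version of the Wechsler Intelligence Scale for Children". Section 2.1 has "clinical indicators, intelligence tests, and questionnaire surveys being conducted at baseline, as well as at 3 and 6 months", so both instruments are scheduled at all three visits.

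Section 3 (Statistical analysis) gives one rule for all of these: "The Mann-Whitney U test will be used to compare changes in each indicator between the two groups at 3 months and 6 months", relative to baseline. It names no covariate. Age is listed among the baseline demographics, which are compared between groups by a chi-square test, and section 2.4 describes simple randomization without stratification by age.

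**The concern.** An infant gains far more length, weight and head circumference in six months than a school-age child does. If raw gains are ranked across birth to under 12 years, much of the ranking reflects the children's ages. The Mann-Whitney test takes no covariate, so that variation stays in the comparison as noise. With about 25 children per arm and no age stratification, a chance difference in age mix also moves the observed difference in growth.

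For development, "compare changes in each indicator between the two groups" puts changes on two different instruments into one ranking. Nothing states that a point on one is comparable with a point on the other. If the instrument is chosen by age at each visit, a child who passes the cut-off would have a baseline on one test and a follow-up on the other, and the difference between them has no meaning.

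At stake is how much these outcomes can show. Section 2.6 names nutrition and intellectual development, beside metabolism, as areas in which effectiveness is explored. A blunted growth comparison could be read as showing no effect when it had a reduced chance of showing one.

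**Working it through.** **The plan's own figure.** Section 2.3 sizes the trial on serum phenylalanine: difference 100, SD 100, two-sided α 0.05, power 90%.
- Normal approximation: 2 × (1.960 + 1.282)² × (100/100)² = 21.0, so 22 per group.
- Two-sample t-test: 22.02, so 23 per group (power 91.2% at 23). This matches the stated 23.
- With 10% attrition, 23/0.9 = 25.6, against the stated 25 per group.

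The figure reproduces closely. No figure is given for growth or development.

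**Growth: inputs.** From the article: ages 0 to under 12, follow-up of 6 months, 23 analysed per group. Assumed, because the article gives no growth data:
- Expected six-month height gain at age a is 3 + (b − 3) × exp(−a/0.8) cm, with b = 8, 12 or 17 cm at birth, falling to 3 cm at school age.
- Residual SD is 1 cm, and the true group effect is 1 cm at every age.
- Ages are either uniform on 0–12 or skewed young (12 × Beta(1,3), mean 3 years).

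**Growth: share of variance due to age, uniform ages.** The mean of exp(−a/0.8) is 0.8/12 = 0.0667 and the mean of its square is 0.4/12 = 0.0333. Its variance is 0.0333 − 0.0667² = 0.0289. The age variance is (b − 3)² × 0.0289, and the share is that value divided by itself plus 1.
- b = 8: 25 × 0.0289 = 0.72; share 0.72/1.72 = 42%
- b = 12: 81 × 0.0289 = 2.34; share 2.34/3.34 = 70%
- b = 17: 196 × 0.0289 = 5.66; share 5.66/6.66 = 85%

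With ages skewed young, the shares are 61%, 84% and 93%.

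**Growth: chance imbalance, uniform ages.** The SD of the between-group difference in mean gain that is due to age alone is √(2 × age variance/23). This gives 0.25, 0.45 and 0.70 cm for the three curves, against the assumed effect of 1 cm.

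**Growth: power.** Simulated Mann-Whitney tests, 23 per group, 3,000 runs per cell:

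| Ages | b (cm) | Power, raw change | Power, age-expected gain removed | Type I error, raw |
|---|---|---|---|---|
| Uniform | 8 | 78% | 89% | 4.6% |
| Uniform | 12 | 71% | 89% | 3.9% |
| Uniform | 17 | 62% | 89% | 5.1% |
| Skewed young | 8 | 60% | 91% | 4.8% |
| Skewed young | 12 | 40% | 90% | 4.5% |
| Skewed young | 17 | 31% | 90% | 4.8% |

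The fourth column removes the age-expected gain exactly, so it is the most that standardisation could recover. Only height was simulated. The same reasoning applies to weight and head circumference, but their size was not computed.

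**Development.** If the instrument follows age at the visit and ages are uniform, 0.5/12 = 4.2% of children pass the cut-off within 6 months. That is 50 × 0.042 = 2.1 children, and the chance of at least one is 1 − (1 − 0.0417)^50 = 88%. If 2% to 8% cross, that is 1 to 4 children, with a chance of at least one of 64% to 98%. If age is fixed at baseline, no child crosses. Under either reading, both instruments fall under the single comparison in section 3.

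**The case against.** The strongest reply is that cm and kg are units in an outcome list, that z-scores are commonly derived under an analysis plan, and that the plan is not shown here. That would answer a complaint about missing detail. But the article itself fixes the metric, the age range and an unadjusted test on change in each indicator, so raw change is the natural reading. A later plan may still derive z-scores, and the text does not forbid it.

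Several stronger readings are tempting, and the document does not support them.
- *That the instrument switches during follow-up.* Sections 2.8 and 3 do not say whether age is taken at baseline or at the visit. Age is listed for collection at baseline only, which fits a baseline rule as well. What stands is the ambiguity and the pooling of two instruments.
- *That age biases the comparison.* Allocation is random. Age adds noise and chance imbalance, and type I error stays at about 5%.
- *That age dominates growth change, or that power is always poor.* At 42% age is not the larger part of the variance. With uniform ages power is still 62–78%; it falls to 31–60% only if the children are mostly young.
- *That growth would reveal harm from the diet itself.* Under section 2.1 control families are also taught the low-phenylalanine diet. The arms differ in mHealth support, so growth would differ through adherence.

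It is also fair to say that these are a few items in a long secondary list, and that holding a child on a scale named for ages 0–6 after the sixth year may not be valid. The fix has to allow for that.

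**Conclusion.** The point holds as a recommendation on secondary outcomes. As written, the growth comparisons carry avoidable noise from age. Under the assumed curves, age accounts for about 42–93% of the variance of six-month height change, and power for a one-residual-SD effect falls from about 90% to somewhere between 31% and 78%, depending on the age mix and the steepness of early growth. The growth curves, the residual SD, the constant effect and the age distributions are all assumptions. The direction of the loss was the same in every case tried.

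The developmental comparison ranks changes on two instruments together without a rule for doing so. Change across instruments is a conditional problem: about 2 of 50 children (range 1–4), and only if age is taken at the visit. The serum phenylalanine comparison and its sample size are not touched.

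**What to change.** **Growth.** State before analysis that height/length, weight and head circumference are converted to age- and sex-standardised z-scores against a named reference, and that change in z-score is compared between groups with adjustment for the baseline z-score. The Mann-Whitney test cannot adjust, so this needs a regression model such as ANCOVA. Age and gender are already collected (Table 2); age should be held precisely enough for infants, for example as date of birth with visit date. Raw cm and kg can still be shown descriptively.

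**Development.** State whether the instrument is set by age at baseline or at the visit. Analyse change within each instrument, or on age-normed standard scores with instrument as a factor. Compute no change across instruments. A child who passes the cut-off and cannot validly stay on the baseline instrument is left out of the change score at that visit, or treated as missing under the multiple imputation already planned in section 3, with baseline age in the imputation model.

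**Cost.** A few sentences and a data conversion, with no new participants or assessments. The price is a handful of developmental change scores lost, about 1 to 4 of 50, and smaller groups wherever the two instruments are analysed separately.
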